
### Participant timeline {13}

All assessment appointments will be scheduled individually, based on participants’ and research team members’ schedules.

After attending the baseline assessment appointment, the participant will be wearing a pedometer for 7 days before starting the intervention. To accommodate all participants enrolled at that time into the timetable of baseline assessment appointment and have their physical activity level measured before the intervention gets started, a period of up to 21 days including the 7-day wearing a pedometer will be allowed between the baseline assessment appointment and the first intervention session. Therefore, the baseline assessment could be carried out between one and 14 days previous to the first intervention session.

After the intervention conclusion, the participant will be wearing a pedometer for 7 days before attending the post-intervention assessment appointment. To accommodate all participants into the post-intervention assessment appointment timetable and have their physical activity level measured before this appointment, a period of up to 21 days including the 7-day wearing a pedometer will be allowed between the intervention conclusion and post-intervention assessment appointment. Therefore, the post-intervention assessment could be carried out between 7 and 21 days after the intervention conclusion.

Upon completing the 6-month follow-up, the participant will be wearing a pedometer for 7 days: (1) after attending the post-follow-up assessment appointment when this appointment is scheduled between 1 and 14 days after the 6-month follow-up completion or (2) before attending the post-follow-up assessment appointment when this appointment is scheduled between 7 and 21 days after 6-month follow-up completion. To accommodate all participants into the post-follow-up assessment appointment schedule and have their physical activity level measured after 6-month follow-up completion, a period of up to 21 days including the 7-day wearing a pedometer will be allowed between the 6-month follow-up completion and post-follow-up assessment appointment. Therefore, the post-follow-up assessment could be carried out between 1 and 14 days after the 6-month follow-up completion.

Table 3 shows the participant timeline.

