*Abbreviations*: *NVS* Newest Vital Sign, *BESES* Bandura's Exercise Self-Efficacy Scale, *MDS* Mediterranean Diet Scale, *MAT ADOs* Brazilian version of the Measure of Adherence to Oral Antidiabetic, *MAT* insulin Insulin Treatments questionnaire, *A1c* glycated hemoglobin, *BMI* Body Mass Index, *HRV* Heart Rate Variability, *iNN* normal RR intervals, *ms* milissegundos, *SDNN* Standard deviation of iNN, *RMSSD* root mean square of the differences between successive iNN, *pNN50* percentage of successive iNN with a duration difference greater than 50ms, *SD1* Poincaré plot standard deviation perpendicular the line of identity, *SD2* Poincaré plot standard deviation along the line of identity, *LF* low-frequency spectral components, *HF* high-frequency spectral components,  *ms²* spectral components in absolute units, *nu*  spectral components in normalized units, *TP* total power

Health literacy, exercise self-efficacy, adherence to the Mediterranean diet, medication adherence, and all cardiometabolic health parameters will be measured during both the baseline and outcomes assessment appointments. Physical activity levels will be measured (1) over the 7 days following the baseline assessment appointment; (2) over the 7 days leading up to the post-intervention assessment appointment; and (3) over the 7 days following the post-follow-up assessment appointment or seven days leading up to this appointment to those participants who kept with them the pedometer worn in the past outcome assessment appointment.

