**Table 3 Tab3:**
[figure not shown]
Overview of the enrollment, interventions and assessments during the trial

t0: 1 to 21-day interval pre-intervention for the baseline assessment, t3: 1 to 21-day interval post-intervention for the post-intervention assessment, t5: 1 to 21-day interval post-follow-up for the post-follow-up assessment

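### The stated baseline visit window (1 to 14 days before the first session) contradicts the pre-intervention pedometer week, and the closing post-follow-up window contradicts the plan's own second option

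*Protocol article*

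**What the plan says.** All of this is in the protocol article.

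**Baseline.** Participant timeline {13} sets the rule: "After attending the baseline assessment appointment, the participant will be wearing a pedometer for 7 days before starting the intervention". It allows up to 21 days, wear week included, between the visit and the first session. It then concludes that "the baseline assessment could be carried out between one and 14 days previous to the first intervention session". The Table 3 footnote gives 1 to 21 days for t0. The Secondary outcomes section defines baseline physical activity as steps recorded "over the 7 days following the baseline assessment appointment", without adding that those days must come before the first session.

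**Post-intervention.** Wear follows the end of the intervention and precedes the visit, and "the post-intervention assessment could be carried out between 7 and 21 days after the intervention conclusion". The footnote has "t3: 1 to 21-day interval post-intervention for the post-intervention assessment".

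**Post-follow-up.** Under option (1) the visit is on days 1 to 14 and wear follows it. Under option (2) wear comes first, "when this appointment is scheduled between 7 and 21 days after 6-month follow-up completion". The section repeats the 21-day allowance but closes with "the post-follow-up assessment could be carried out between 1 and 14 days after the 6-month follow-up completion". The footnote gives 1 to 21 days for t5.

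**The concern.** At baseline the concluding window is presented as following from the wear rule and the allowance, but it does not follow from them. Its lower end is too short to hold the wear week, and its upper end cuts off lead times that the allowance permits. At post-follow-up, a visit on days 15 to 21 is inside one sentence and outside another.

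The baseline slip can reach the data. Steps are a secondary outcome, and the statistical methods compare baseline with post-intervention in a 2 × 2 ANOVA with post hoc pairwise comparisons. Both arms start a program aimed at 150 minutes or more of aerobic exercise a week, mainly walking. A coordinator who schedules by the stated window, and an analyst who takes the 7 days after the visit as baseline, could together count program walking as baseline activity. That would shrink the measured change in each arm.

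**Working it through.** **Inputs.** Wear period of 7 days and allowance of 21 days (Participant timeline {13}); baseline steps taken as the 7 days after the visit (Secondary outcomes); stated windows from the timeline text and the Table 3 footnote.

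**1. Can the stated 1 to 14 days be reproduced?** The figure 14 is 21 − 7. That subtraction is right when visits fill the start of a 21-day block and wear follows, as in follow-up option (1): the latest visit is day 14, and 14 + 7 = 21. It does not give days before the first session. If a 21-day block ends just before session 1, block day b lies 22 − b days before it. Block days 1 to 14 are then lead times of 21 down to 8 days. So 1 to 14 can be a position in the block, but not the lead time that the sentence claims.

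**2. Lead time implied by the rule.** Let the visit be D days before session 1. Seven wear days must finish before session 1, so D ≥ 7 if the visit day counts as a wear day, or D ≥ 8 if wear starts the next day. The allowance gives D ≤ 21. The implied window is 7 to 21 days (or 8 to 21). Against the stated 1 to 14:
- days 1 to 6 are admitted but cannot hold the wear week;
- days 7 to 14 agree (day 7 only if the visit day counts);
- days 15 to 21 are allowed by the 21-day rule but excluded.

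**3. Wear days falling on or after session 1.** The number is max(0, 7 − D) if wear starts on the visit day, and max(0, 8 − D) if it starts the next day.

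| D (days before session 1) | Wear starts on visit day | Wear starts next day |
|---|---|---|
| 1 | 6 | 7 |
| 2 | 5 | 6 |
| 3 | 4 | 5 |
| 4 | 3 | 4 |
| 5 | 2 | 3 |
| 6 | 1 | 2 |
| 7 | 0 | 1 |
| 8 or more | 0 | 0 |

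**4. Post-intervention.** Take the last intervention day as day 0 and the visit as day D. The same formulas count wear days on or before day 0. Over the text window of 7 to 21 days the overlap is 0, apart from 1 day at D = 7 if the visit day is not a wear day. Rule and window agree. Visits on days 1 to 6 arise only if the footnote's 1 to 21 days is read as the visit window.

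**5. Post-follow-up.** Option (1) covers days 1 to 14 and option (2) days 7 to 21; together they span 1 to 21. The closing sentence omits days 15 to 21. No pedometer day here overlaps the intervention.

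**The case against.** The best reply is that the intention is clear. The timeline states that baseline activity is measured before the intervention begins, so a visit 1 to 6 days ahead followed by a full week of wear would breach an explicit sentence. On this view the window is a slip in derivation that harms nothing if sites follow the rule. This stands in part. A reader might infer that the plan permits baseline wear during the program, but it does not: it contradicts itself. The slip still matters because the outcome definition does not repeat the requirement and would not catch a late visit.

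A reader might also infer from the Table 3 footnote that post-intervention steps may be recorded during the program. The documents do not support that. The text places wear after the intervention and sets a matching 7 to 21 days. The footnote's 1 to 21 days can describe the whole assessment interval, with wear from day 1 and a visit by day 21. The t0 and t5 footnotes can be read in the same way. The body of Table 3 is not available to settle it.

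A reader might put a large figure on the distortion. If 150 minutes of walking at an assumed 90 to 110 steps per minute fell wholly inside the baseline week, it would add 150 × 90 / 7 ≈ 1,929 to 150 × 110 / 7 ≈ 2,357 steps a day. That is a worst case: full overlap, the full target met in week 1, and all of it extra walking. The cadence is not in the documents.

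Finally, both arms follow the same exercise program under the same scheduling rule, so a common shift in baseline largely cancels between arms. That stands. So does the point that no sentence excludes an out-of-window follow-up visit from analysis.

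**Conclusion.** Two sentences in Participant timeline {13} are wrong as written. The baseline window of 1 to 14 days conflicts with a rule that implies about 7 to 21. The closing post-follow-up window of 1 to 14 days conflicts with option (2) and the 21-day allowance. The post-intervention text is sound and differs only from an ambiguous footnote.

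At baseline, 6 of the 14 stated lead times cannot hold the wear week, with 1 to 7 pedometer days falling inside the program depending on the lead time and the counting convention. These are calendar options, not participants: the documents do not show how many visits fell there, possibly none. The effect is limited to one secondary outcome and mainly to its within-arm change. Bias between arms would need the overlap, or the early response to the program, to differ by arm, and nothing in the documents shows that. The primary outcomes are not affected. The conclusion rests on reading the stated window as visit days counted back from the first session, which is what the sentence says.

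**What to change.** **Wording.** Restate the baseline window so that it agrees with the wear rule and the 21-day allowance, and say whether the visit day counts as a wear day. Extend the closing post-follow-up sentence to cover both options. State in the Table 3 footnote whether each interval is the visit window or includes the wear days.

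**Analysis, settled before it is run.** Using recorded dates, count as baseline only pedometer days before the first session, and report how many participants had fewer than 7. Analyse mean steps per day over the eligible days. Restrict total steps per week to participants with 7 eligible days, or scale it as 7 × the daily mean. Keep follow-up visits made under either option.

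**Cost.** Text edits and a date check; no new data are needed. Recruitment has ended, so baseline scheduling itself cannot be changed. Participants with late baseline visits contribute fewer than 7 days, which loses a little precision and slightly alters the seven-day outcome definition in Table 2. That change should be declared.

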**Table 3 Tab3:**
[figure not shown]
Overview of the enrollment, interventions and assessments during the trial

t0: 1 to 21-day interval pre-intervention for the baseline assessment, t3: 1 to 21-day interval post-intervention for the post-intervention assessment, t5: 1 to 21-day interval post-follow-up for the post-follow-up assessment

### Sample size {14}

The sample size was calculated considering the ISWT distance as the primary outcome, using parameters derived from a previous study involving educational intervention in cardiac rehabilitation [50]. The calculation was performed using R Software version 3.4.3, with the following parameters: a moderate effect size (*d* = 0.20), 80% statistical power, a 5% alpha level, one-sided test, two arms, and three measurements. A total sample size of 200 participants (100 per arm) was determined. Assuming a 20% attrition rate, based on a previous study [50], 120 participants would be enrolled in each arm to ensure that 200 participants complete the study protocol.

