#### Primary and secondary outcomes

Primary and secondary outcomes will be presented as central tendency and dispersion measures. Data distribution will be analyzed using the Shapiro–Wilk test. The analysis of variance (2 × 2 ANOVA) will compare data between baseline and post-intervention and between groups. An alpha of 5% will be considered for statistical significance, and post hoc comparisons will be performed to detect two-by-two differences. In case of missing data, the statistical procedures will follow the intention to treat.

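### The 80% power claimed for d = 0.20 with 100 per arm rests on an unstated model and correlation, and does not match the planned 2 × 2 ANOVA

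*Protocol article*

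**What the plan says.** The section Sample size {14} of the protocol article sizes the trial on walking distance: "The sample size was calculated considering the ISWT distance as the primary outcome". The inputs are an effect called moderate, with d = "0.20), 80% statistical power, a 5% alpha level, one-sided test, two arms, and three measurements". The result is: "A total sample size of 200 participants (100 per arm) was determined". The section names R as the software and an earlier educational trial in cardiac rehabilitation as the source of the parameters. It gives no standard deviation, no correlation between the three measurements and no model.

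The section on the analysis of primary and secondary outcomes says: "The analysis of variance (2 × 2 ANOVA) will compare data between baseline and post-intervention and between groups". It sets alpha at 5% without stating sidedness. The 6-month follow-up measurement is not part of the comparison it describes.

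**The concern.** Three features of the paragraph do not fit together. A standardised difference of 0.20 is conventionally small, yet it is called moderate. One hundred per arm is far below what a plain two-arm comparison needs at d = 0.20. The calculation is one-sided with three measurements, while the planned ANOVA F-test is non-directional and uses two time points.

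What is at stake is what the trial can claim to detect on a primary outcome. Recruitment ended in February 2024 (Trial status), so the sample is fixed. If the planned test has much less than 80% power at 0.20 SD, a non-significant walking-distance result says little about an effect of that size, while the published power statement suggests otherwise.

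**Working it through.** **Inputs from the document.** d = 0.20; power 80%; alpha 5%; one-sided; two arms at 1:1; three measurements; 100 completers per arm (taken as given). **Input not in the document.** The correlation ρ between measurements, assumed common to all pairs and varied below.

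**1. Plain two-arm comparison.** n per arm = 2(z₁₋α + z₀.₈)²/d².
- One-sided: 2(1.645 + 0.842)²/0.04 ≈ 309.1, so 310 per arm.
- Two-sided: 2(1.960 + 0.842)²/0.04 ≈ 392.4, so 393 per arm (394 by the t-test).
- With 100 per arm, t-test power is 41% one-sided and 29% two-sided.

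The stated 100 per arm is not reproduced this way.

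**2. Using the three measurements.** For 100 per arm at d = 0.20 one-sided, the variance factor must be 100/309.1 = 0.323.

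| Model, one-sided, d = 0.20 | Variance factor | n per arm at ρ = 0.5 / 0.7 / 0.8 | ρ giving 100 per arm |
|---|---|---|---|
| ANCOVA, mean of two post values | (1+ρ)/2 − ρ² | 155 / 111 / 80 | about 0.74 |
| ANCOVA, one post value | 1 − ρ² | 232 / 158 / 111 | about 0.82 |
| Change score, baseline to post | 2(1−ρ) | 309 / 186 / 124 | about 0.84 |

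So the stated figure can be reached, but only with an unstated model and a fairly high unstated ρ.

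**3. The planned analysis.** With two groups and two time points, the group-by-time test of the 2 × 2 ANOVA equals a t-test on the change score. The effective standardised difference is 0.20/√[2(1−ρ)]. With 100 per arm:

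| ρ | Effective difference | Two-sided power | One-sided power |
|---|---|---|---|
| 0.5 | 0.200 | 29% | 41% |
| 0.7 | 0.258 | 44% | 57% |
| 0.8 | 0.316 | 60% | 72% |

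Power of 80% needs ρ of about 0.87 two-sided or about 0.84 one-sided.

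**4. Detectable effect with 100 per arm at 80% power.** For a post score, or a change score with ρ = 0.5, it is d ≈ 0.40 two-sided and 0.35 one-sided. For the change score in general, multiply by √[2(1−ρ)]. Two-sided this gives 0.40 × 0.775 ≈ 0.31 at ρ = 0.7 and 0.40 × 0.632 ≈ 0.25 at ρ = 0.8.

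**5. Other specifications that return about 200 in total.**
- d = 0.40, two-sided: 99.08 per arm by the t-test, so 100. For two groups f = d/2, so this is the F-test with f = 0.20 (total 198.2).
- Repeated-measures group-by-time F-test with f = 0.10: total 200 with two measurements at ρ = 0.5. Its noncentrality is 0.10² × 200 × 2/(1 − 0.5) = 8. The change-score test gives (200/4)δ²/[2(1 − 0.5)] = 8, so δ = 0.40. This route also implies a 0.40 SD difference in change.
- The same F-test with three measurements: total 196 at ρ = 0.4.

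More than one route leads to the stated total, and the document does not say which was used.

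**The case against.** The strongest defence is that three measurements are a stated input and that a single-measurement t-test is not what the section describes. This stands. A reader might infer from the 310 per arm that the stated inputs cannot give 100 and that 80% power at d = 0.20 is simply false. The document does not support that: step 2 shows a baseline-adjusted model that reaches 100 per arm at ρ of about 0.74.

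A reader might also conclude that an f was certainly mislabelled as d. The match with f = 0.20 and the word moderate point that way, but step 5 shows other routes, and the source of the parameters is not available here. It would therefore be unsafe to have the sponsor write d = 0.40 into the plan as the original assumption without checking.

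It is also fair to say that a journal article may leave the correlation and the R function to the full protocol, so their absence alone is no fault. And an ANOVA F-test is non-directional by construction, so the analysis section is not really ambiguous about sidedness.

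None of this removes the mismatch. Both sections are in the text. One sizes a one-sided test on three measurements; the other plans a non-directional test on two. The models that reach 100 per arm at moderate ρ are not the planned one.

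**Conclusion.** The concern holds in this form: the power statement cannot be verified from its listed inputs, and it does not apply to the analysis the article plans. Under the group-by-time test of the 2 × 2 ANOVA, two-sided power at d = 0.20 with 100 completers per arm is about 29% to 60% for ρ from 0.5 to 0.8, and it reaches 80% only at ρ of about 0.87. These figures assume equal variances at the two time points, d scaled to the SD of a single measurement, and no loss below 100 per arm. The result depends strongly on ρ, which the document does not give. That the effect size was really f = 0.20 is plausible and unproven.

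**What to change.** Restate the sample-size paragraph for the analysis actually planned:
- Name the effect-size metric (d or f), the assumed correlation and the model.
- Give the power or detectable effect that follows. With 100 completers per arm and two-sided 5%, the effect detectable with 80% power is d of about 0.40 for a post score, or for a change score with ρ = 0.5.
- If the sponsor's records show that the calculation used f = 0.20, say so and give the equivalent d = 0.40. If d = 0.20 was intended, report the power of the planned test at the assumed ρ.
- Align sidedness (two-sided 5%, as the F-test implies) and the number of time points between the sample-size and analysis sections.

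This is a change of text after checking the original R calculation. It needs no extra participants. The cost is that the stated detectable effect will probably be less favourable than 0.20.

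### The 80% power for ISWT distance is stated for a one-sided 5% test, but the planned 2 × 2 ANOVA at 5% is two-sided, so the stated power is not that of the planned test

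*Protocol article*

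**What the plan says.** Under Sample size {14} the protocol article names the endpoint behind the calculation: "The sample size was calculated considering the ISWT distance as the primary outcome". The inputs are "a moderate effect size (*d* = 0.20") and "80% statistical power, a 5% alpha level, one-sided test, two arms, and three measurements". The result is given as "A total sample size of 200 participants (100 per arm) was determined". No standard deviation, difference in metres or correlation between measurements is reported.

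Under Statistical methods, Primary and secondary outcomes, the same endpoint is analysed as follows: "The analysis of variance (2 × 2 ANOVA) will compare data between baseline and post-intervention and between groups". The criterion is "An alpha of 5% will be considered for statistical significance, and post hoc comparisons will be performed to detect two-by-two differences". The article does not mention a one-sided contrast, a halved p-value or any other directional rule, and no section links the ANOVA back to the one-sided sizing.

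**The concern.** Power is a property of a particular test at a particular critical value. A one-sided 5% test has the same critical value as a two-sided 10% test. The ANOVA named in the analysis section has two groups and two time points, so its group, time and group-by-time effects each have one numerator degree of freedom. For such an effect F is the square of a t statistic. The F test therefore rejects for a difference in either direction and, at 5%, places 2.5% in the direction favouring the education arm.

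The sizing and analysis sections thus describe different tests of the same primary outcome. A reader who takes 80% as the chance that the planned analysis detects the assumed ISWT effect is relying on a figure stated for a more lenient test. This conflict would remain if the effect size or the correlation were clarified, because it lies in the sidedness alone.

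**Working it through.** **Inputs.** From Sample size {14}: alpha 0.05, one-sided, power 0.80, d = 0.20, two arms, three measurements, 100 per arm. From Primary and secondary outcomes: 2 × 2 ANOVA, alpha 0.05. Normal quantiles: 1.645 (one-sided 5%), 1.960 (two-sided 5%), 0.842 (80% power).

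**Step 1. Can the stated 100 per arm be reproduced?** For a plain comparison of two means, n per arm = 2(z_alpha + z_power)² / d².
- One-sided: 2(1.645 + 0.842)² / 0.20² gives 310 per arm.
- Two-sided: 2(1.960 + 0.842)² / 0.20² gives 393 per arm.
- At 100 per arm the noncentrality is 0.20 × √(100/2) = 1.414. Power is Φ(1.414 − 1.645) = 41% one-sided and Φ(1.414 − 1.960) = 29% two-sided.

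The stated figure is not reproduced this way.

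**Step 2. Does using three measurements explain it?** Only with a correlation r that the article does not give.
- Mean of two follow-up visits adjusted for baseline: the variance factor is (1 + r)/2 − r². This is 0.36 at r = 0.7 and 0.26 at r = 0.8. One-sided n is 112 and 81 per arm respectively. Two-sided n at r = 0.8 is 103.
- Mean of all three measurements: the variance factor is (1 + 2r)/3. One-sided n is 104 at r = 0 and larger for any positive r.

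A suitable r could therefore bring either sidedness to about 100 per arm, so the sample size does not show which test was used.

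**Step 3. Is there a reading that gives 100 directly?** If 0.20 is Cohen's f, then with two equal groups d = 2f = 0.40.
- The exact two-sided F test at 5% first reaches 80% at 100 per arm, with power 80.4%.
- The one-sided version needs 78 per arm and has 88.0% power at 100.

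On this reading the stated size matches the two-sided test, not the one-sided one.

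**Step 4. What does the change of sidedness cost if the article's description is accurate?** For a single one-degree-of-freedom contrast with exactly 80% one-sided power:
- Noncentrality = 1.645 + 0.842 = 2.486 (from unrounded quantiles).
- Two-sided 5% power = Φ(2.486 − 1.960) = 0.701. A noncentral t with 198 degrees of freedom gives 0.699.
- Sample-size ratio to regain 80% = (1.960 + 0.842)² / (1.645 + 0.842)² = 1.27, or about 127 per arm instead of 100.

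**Step 5. Where would the two tests differ?** With 198 degrees of freedom the critical t is 1.653 one-sided and 1.972 two-sided. Multiplied by √(2/100), these are differences of about 0.234 and 0.279 standard deviations. A favourable result in between has a two-sided p-value between 0.05 and 0.10.

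**The case against.** The strongest reply has four parts.

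- **The hypothesis is directional, so one-sided sizing is legitimate.** The background does predict superiority of the combined programme, and that could justify a one-sided test. But the test named for the analysis is an F test, which is not one-sided, so the two sections would still need reconciling.
- **Sidedness may be left to a statistical analysis plan.** This would answer a complaint about missing detail. Here the article itself fixes a one-sided basis in one section and a two-sided test in another, so a later plan would have to depart from one of them.
- **The loss to 70% is not established.** This stands. It assumes that the one-sided calculation was actually run on a single one-degree-of-freedom contrast and gave exactly 80%. The sizing cites three measurements, and a group-by-time F test over three measurements has two numerator degrees of freedom and no one-sided form. A reader might infer that the trial is underpowered at 70%. The article does not support that: 100 per arm also matches a two-sided F test with f = 0.20, in which case the one-sided label may simply be a misdescription.
- **No decision rule is in conflict.** This also stands. A reader might infer that a borderline ISWT result, with t between about 1.65 and 1.97, has two possible verdicts, or that the false-positive risk in favour of the education arm is doubled. The sample size section only lists inputs to a calculation. The analysis section alone sets a significance criterion, and under it such a result is not significant. Reaching the other verdict would mean departing from the stated analysis, which the article nowhere proposes.

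**Conclusion.** The inconsistency is in the text: the 80% is stated for a one-sided 5% test, and the planned ANOVA is two-sided at 5%. The stated power is therefore not the power of the planned test as the article describes the two.

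The size of the discrepancy is conditional. It is about 10 percentage points (80% to about 70%, or 1.27 times the participants to recover) if the one-sided calculation was truly used on a single one-degree-of-freedom contrast. It is nil if 0.20 was Cohen's f in a two-sided F test, where power at 100 per arm is about 80%. If d = 0.20 was meant for a plain comparison of means, power is far below 80% under either sidedness (about 41% and 29%). The article does not give enough to choose among these. What is established is that the sizing statement needs correcting or explaining, not that the trial has any particular shortfall in power.

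**What to change.** Before database lock:

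- State that the primary between-arm comparison is tested two-sided at 5% and reported with a 95% confidence interval, as the ANOVA already implies.
- Remove the one-sided wording from Sample size {14}.
- Say whether 0.20 is d or f, and which model and correlation between measurements produced 100 per arm.
- Restate the power of the two-sided test from those inputs: about 70% if the one-sided calculation was truly used, otherwise the recalculated figure. The 70% should not be printed without that check.

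The cost is wording in two sections and one recalculation. Recruitment ended in February 2024, and no extra participants or data are required. The downside is that the stated power may become less favourable.

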### Trial design {8}

This is a double-blinded (both outcomes’ assessors and data analysts) multicenter randomized controlled trial featuring two-arm parallel groups over 9 months (comprising a 12-week intervention period followed by a 6-month follow-up) with a 1:1 allocation ratio that follows the SPIRIT reporting guidelines [32].

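### At the plan's own 20% attrition, enrolling 120 per arm is expected to leave 192 completers, not 200: a small inflation error to be restated

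*Protocol article*

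**What the plan says.** The statement is in the Protocol article, Sample size {14}. The calculation takes the incremental shuttle walk distance as the outcome, with d = 0.20 and "80% statistical power, a 5% alpha level, one-sided test, two arms, and three measurements". Its result is: "A total sample size of 200 participants (100 per arm) was determined". The allowance for loss follows directly: "Assuming a 20% attrition rate, based on a previous study" of an educational intervention in cardiac rehabilitation. The conclusion is that "120 participants would be enrolled in each arm to ensure that 200 participants complete the study protocol". Trial design {8} sets 1:1 allocation, so 120 per arm is 240 in total. No other section gives a different attrition rate or enrolment target.

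**The concern.** The passage gives the number needed, the loss rate and the number to enrol, and then says what the enrolment will achieve. Any reader can check that last step, and it fails. Enrolment was raised by 20% of the number needed, but attrition acts on the number enrolled. A 20% loss from 120 is 24 people, while the allowance covers only 20.

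At stake is the accuracy of the sample size justification. The 80% power is attached to 200 participants, and the text says that 240 enrolled will secure them. Left as it is, the statement is likely to be carried into the results report.

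**Working it through.** **Inputs, all from Sample size {14}:** 100 required per arm (200 in total); attrition 20%; 120 enrolled per arm (240 in total); alpha 5%, one-sided; power 80%.

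**Reproducing the plan's figure.** Required number x (1 + attrition) = 100 x 1.20 = 120 per arm. This gives the stated enrolment, so multiplication appears to be the method used.

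**Standard inflation.** Required number / (1 - attrition) = 100 / 0.80 = 125 per arm, or 250 in total. The plan's 240 is 10 below this.

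**Expected completers under the plan.** Enrolled x (1 - attrition) = 120 x 0.80 = 96 per arm, and 240 x 0.80 = 192 in total. The shortfall against 200 is 8, or 4 per arm (8 / 200 = 4%).

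**Attrition that 240 can absorb.** 1 - 200/240 = 16.7%.

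**Chance of reaching the target.** If each of 240 participants is lost independently with probability 0.20, the exact binomial probability of at least 200 completers is about 11%. The claim to ensure 200 is therefore not met at the plan's own rate.

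**Effect on power, conditional on the base figure.** Suppose 100 per arm gives exactly 80% power at one-sided 5%. The standardised signal is then 1.645 + 0.842 = 2.487. It scales with the square root of the sample size, so at 96 per arm it is 2.487 x sqrt(0.96) = 2.436. Power is Phi(2.436 - 1.645) = Phi(0.791) = 78.6%. A two-sided 5% test under the same condition gives 78.4%. The loss is about 1.4 to 1.6 percentage points.

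**Why this is conditional.** The base 200 cannot be confirmed from the stated parameters. A plain two-sample comparison at d = 0.20, one-sided 5% and 80% power needs 310 per arm, and has about 41% power at 100 per arm. A repeated-measures calculation needs a within-person correlation, which the section does not give. The attrition arithmetic does not depend on this: however 200 was obtained, 240 enrolled with 20% lost is not expected to deliver it.

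**The case against.** The strongest reply is that the error hardly matters. Eight completers in 200 is 4%, the conditional loss of power is about 1.5 points, and the 20% is only a planning value borrowed from another population. If actual attrition is 16.7% or lower, 200 will complete. Trial status reports that recruitment ended in February 2024, so enrolment cannot be raised on this account. All of this stands, and it is why the point is minor.

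One could also read the 20% as an over-recruitment margin, which would make 120 correct. The text calls it an attrition rate, however, and names the number who will complete, so that reading does not fit.

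A reader might go further and infer that the trial misses its 80% power because of this slip, or that the protocol should now state about 79% power. The document supports neither. The inference requires attrition of exactly 20%, a completers-only analysis, and acceptance that 100 per arm gives 80%. The statistical sections (Primary and secondary outcomes; Methods {20c}) instead plan an intention-to-treat analysis with missing values replaced by zero. All 240 would then enter, and whatever the merits of that imputation, power would not be a simple function of the number completing. A setting such as d = 0.40, two-sided, does return about 80% at 100 per arm (80.4%, falling to 78.7% at 96), but the plan states d = 0.20, one-sided, with three measurements. Power from a setting chosen because it fits should not be attributed to the plan.

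**Conclusion.** The point holds as an arithmetic error of minor consequence. The assumed 20% attrition and the promised 200 completers cannot both stand with 240 enrolled. The shortfall of 8 expected completers and the 16.7% limit follow from the plan's figures alone. The 78.6% power figure does not: it assumes that 100 per arm gives 80% and that only completers are analysed. It should be read as a guide to how small the effect is, not as the power of the trial. The error changes nothing in the trial's design, conduct or analysis.

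**What to change.** Replace the sentence in Sample size {14} with one of these:

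- *240 enrolled; at 20% attrition 192 (96 per arm) are expected to complete, slightly below the 200 calculated.*
- *Enrolling 240 retains 200 completers if attrition is at most 16.7%.*

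Do not add an unconditional power figure of 79%. Beside d = 0.20, one-sided, it would be a value that the stated parameters have not been shown to support. If power is restated, say in the same sentence that it assumes 100 per arm gives 80%. The results report should give the actual number completing in each arm.

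The cost is one sentence. Enrolment, conduct and analysis are unaffected; the only loss is a slightly less favourable statement of expected completers.
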